### Study Endpoints

ICD-9 codes for primary and secondary endpoints can be seen in Table 1. They will be captured from CMBD-HA database.

#### Primary Endpoint

The primary endpoint will be a composite endpoint of all-cause mortality, ACS and ischaemic stroke. From the index date (first episode of ACS), patients will be followed up to the end of follow-up or until a new diagnosis of any of the endpoints stated above. Patients who experience more than one endpoint during the study follow-up will be censored upon the first event of interest. Patients who do not experience any of the clinical events included in the composite endpoint during the follow-up will be censored at the last date of follow-up.

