### Study Population

The study population includes individuals ≥18 years with an incident diagnosis of ACS during the study period 2006-2015, with at least two months of follow-up in the Information System for Research in Primary Care (SIDIAP) [12] after the index date. The next patients will be excluded: pregnant women on the index date; patients with a recorded diagnosis of ischaemic stroke in the six months prior to index date; patients living in a nursing home on the index date; and patients with Alzheimer’s disease or other dementias.

Case definition: patient with an incident diagnosis of ACS registered in CMBD-HA (dataset of diagnoses at hospital discharge) [13] of the Catalan Health Institute (ICS) within the period from 2006-2015. Index date definition: date of ACS episode.

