#### Adherence Definition

To estimate medication adherence, we will calculate the PDC for all four study treatments during eight months of follow-up after the index date. The PDC calculation is based on the packages dispensed and days of supply for each package, considering that the number of tablets contained in one package covers the treatment necessary for 28 or 30 days, depending on the drug. The information will be obtained from the pharmacy invoice data. For the PDC calculation, the numerator is the number of packages dispensed (invoice register) during the first 8 months of follow-up, and the denominator is the period of 8 months, which is the period for the adherence measure. Based on the PDC, patient adherence to each study drug is usually classified into one of two categories using the standard threshold of 75% (≥75%: adherent, <75%: nonadherent) [6,9]. PDC=75% accounts for six packages (each one including one month of drug treatment) dispensed during eight months. We define adherent patients as those who have received at least six packages during the first eight months after the event. Finally, according to adherence to all four study drugs, patients will be classified as adherent if they get the refill for all study drugs: PDC antiplatelet ≥75% + PDC beta-blockers ≥75% + PDC ACEI/ARB ≥75% + PDC statin ≥75%.

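### Adherence is measured over the first eight months after the ACS but the Cox clock starts at the ACS, so early deaths are counted as nonadherent (immortal time bias)

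*Protocol article*

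**What the plan says.** All statements are in the Protocol article.

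- **Time zero.** Study Population: "Index date definition: date of ACS episode". Primary Endpoint: "From the index date (first episode of ACS), patients will be followed up to the end of follow-up", or until a first death, ACS or ischaemic stroke.
- **Exposure.** Adherence Definition: "We define adherent patients as those who have received at least six packages during the first eight months after the event". This applies to each of the four drug groups: "patients will be classified as adherent if they get the refill for all study drugs".
- **Denominator.** Adherence Definition: "the denominator is the period of 8 months, which is the period for the adherence measure". It is not shortened for patients who die or leave.
- **Entry.** Study Population: patients "with at least two months of follow-up in the Information System for Research in Primary Care" after the index date.
- **Model.** Statistical analysis: raw and adjusted HRs for adherence from Cox models. No landmark, delayed entry or time-dependent exposure is stated.
- **Limitations.** The Discussion names missing data and confounding only.

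**The concern.** The exposure group is known only at month 8, but events are counted against it from day 0. Three things follow.

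1. A patient who dies between month 2 and about month 5 cannot normally have six packages of each drug, and so is nonadherent however well the drugs were taken.
2. A patient classed as adherent has, in effect, been guaranteed survival to the sixth refill.
3. A non-fatal ACS or stroke before month 8 comes before the end of exposure measurement. If later dispensing counts, exposure is partly measured after the outcome and may be changed by it. If it does not count, the patient is forced into the nonadherent group.

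The first two effects lower the HR for adherence without any drug benefit. So does the third if later dispensing is ignored. The Conclusions, Results and Discussion all expect lower risk in adherent patients, so the bias imitates the hypothesis. All-cause mortality, a secondary endpoint, is hit hardest. Secondary objective 1 is exposed too: a patient who dies before any sixth package falls into the no-drug category, which can produce a false gradient by number of drugs.

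**Working it through.** **The plan's own figures.** The adherence threshold is 6/8 = 75%, as stated. The expected sample in Sample Size also reproduces: 3415 / 3 years × 10 years × 0.30 = 3415, stated as about 3400. No event rate, target HR or all-four adherence rate is given, so the size of the bias has to be shown over assumptions.

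**When adherence can first be reached.** With one package at a time from day 0 and no stockpiling, the sixth is dispensed at 5 × 28 = day 140 or 5 × 30 = day 150. A fully compliant patient who dies at month 3 (about day 91) has had at most four packages: 4/8 = 50%, nonadherent.

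**Size, by approximation.** Let p be the proportion who would be adherent if they lived long enough. Let e be the share of all events that fall before adherence can be reached and so force nonadherence. Under no true effect, a fraction e of the would-be adherent patients' events moves to the nonadherent group. Ignoring the little person-time that moves with them:

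spurious HR ≈ (1 − e) / (1 + e·p/(1 − p))

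**Size, by simulation with true HR = 1.** Assumptions, not in the protocol:
- event hazard 5–10% a year after month 8 and 5–30% before
- p = 20% or 45%
- 40% of events fatal
- 2% a year lost to follow-up
- entry uniform over 2006–2015, follow-up to the end of 2016
- patients with an event or loss before two months removed, which is somewhat stricter than the protocol's entry rule

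Four scenarios set against the formula:

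| p | Events forcing nonadherence | e | Formula | Simulated HR |
|---|---|---|---|---|
| 0.20 | any, before day 150 | 0.134 | 0.866 / 1.034 = 0.84 | 0.837 |
| 0.45 | any, before day 150 | 0.135 | 0.865 / 1.110 = 0.78 | 0.781 |
| 0.45 | any, before month 8 | 0.267 | 0.733 / 1.218 = 0.60 | 0.612 |
| 0.20 | fatal only, before day 150 | 0.4 × 0.133 = 0.053 | 0.947 / 1.013 = 0.93 | 0.933 |

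Over all scenarios, with rejection rates at N = 3400 (300 runs each, nominal 5%):

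| Reading of the definition | Spurious composite HR | False-positive rate |
|---|---|---|
| Only deaths and losses before day 150 force nonadherence | 0.89–0.98 | 6–55% |
| Any event or loss before day 150 does | 0.76–0.94 | 9–100% |
| Any event or loss before month 8 does | 0.57–0.87 | 26–100% |
| Clock started at month 8 (landmark) | 0.99–1.01 | 3–8% |

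**A second simulation with different assumptions** used 20 cohorts of 20,000, 25–45% truly adherent, censoring uniform on 12–132 months, survival beyond two months required, and the sixth refill uniform on 5–7.5 months:

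| Deaths in months 2–8 | Composite events by month 8 | Spurious composite HR | Spurious death HR |
|---|---|---|---|
| 2% | 7% | 0.93–0.94 | 0.85–0.89 |
| 4% | 12% | 0.89–0.92 | 0.78–0.83 |
| 6% | 15% | 0.85–0.89 | 0.72–0.79 |

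The landmark analysis gave 1.00–1.01 throughout.

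**Scale.** The post-infarction cohort cited in the Introduction reports adjusted HRs of 0.81 (full versus partial adherence) and 0.72 (full versus nonadherence). Its adherence categories and drugs differ from this protocol's, so the comparison is loose.

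**The case against.** The strongest objection concerns size. No early event rate is given. If only deaths and losses before day 150 force nonadherence, the composite HR may be as mild as 0.98, with a false-positive rate near nominal. An artefact of 0.85–0.94 would explain part of an effect of 0.72–0.81, not all of it. This stands: the size is uncertain, and the largest death-only values belong to a secondary endpoint.

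Four points of detail also stand but do not remove the fault.

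- Patients who leave SIDIAP early are misclassified, but they add event-free time to the nonadherent group and slightly dilute the bias. Early events drive it.
- The two-month entry rule removes the earliest deaths. The death-free time it creates does not itself move a Cox HR, which depends only on risk sets at event times. Starting the clock at month 2 left a simulated death HR at 0.840. The rule does affect incidence rates counted from day 0.
- The definition counts packages without a monthly limit, so bulk dispensing could let a few early deaths qualify as adherent.
- A landmark changes the question to event-free eight-month survivors. Time-updated adherence from the index date keeps the early events and could reasonably be primary instead.

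That a fuller plan might specify a landmark does not answer the point. The article states the exposure window, the denominator and the start of follow-up outright, and a landmark would contradict the Primary Endpoint section. Nor do the stated safeguards help: covariate adjustment, imputation and a proportional-hazards test do not realign exposure and follow-up.

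**Conclusion.** The concern holds. Followed as written, the protocol gives a primary HR biased in favour of adherence. The direction follows from the definitions alone. The size depends on assumed early event rates, the proportion adherent to all four groups, and how dispensing after a non-fatal event is treated. Across the simulations the spurious composite HR runs from 0.98 down to 0.57. With only deaths and losses before day 150 forcing nonadherence it is 0.89–0.98. For all-cause death the second simulation gives 0.72–0.89. On many of these assumptions the artefact is a material share of the effect sought, and an observed HR below 1 could not be read as support for the hypothesis without realigning time zero. This must be fixed before analysis.

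**What to change.** Make an eight-month landmark the primary analysis.

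- **Adherence Definition:** keep the months 0–8 window and the six-package rule.
- **Primary Endpoint:** start the Cox clock at month 8, in patients who at that date are alive, still registered in SIDIAP and free of a new ACS or ischaemic stroke.
- **Early events:** report those in months 0–8 descriptively, by number of study drug groups prescribed.
- **Secondary analyses:** use the same start for the secondary event endpoints and for secondary objective 1.
- **Sensitivity analysis:** start at the index date with adherence as a lagged, time-updated covariate built only from past dispensing. This keeps the early events and shows whether the conclusion depends on dropping them.
- **Discussion:** name immortal time bias and how it is handled.

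The cost is analysis wording; the data are already held. Early events leave the primary HR and the conclusion applies to eight-month event-free survivors. If 7–15% have a composite event by month 8, as assumed in the second simulation, that is 0.07 × 3400 = 238 to 0.15 × 3400 = 510 patients, plus early losses. The protocol gives no rate from which to compute the true number. The landmark does not address confounding between adherent and nonadherent patients, which still needs the planned adjustment.

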#### Secondary Endpoints

The secondary endpoints will be AMI, unstable angina, ischaemic stroke, all-cause mortality, overall number of days on sickness leave due to any cause and due to CVD events, prevalence of use of the four pharmacological groups of interest, posology of the four pharmacological groups of interest.

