The main objective of our study is to assess the relationship between adherences to the four pharmacological groups recommended for secondary prevention and the clinical outcomes of cardiovascular morbidity and mortality in patients with established CHD. The outcomes which are included as components of the composite endpoint are all-cause mortality, ACS, and ischaemic stroke. The secondary objectives are: 1) to assess the incidence of the composite endpoint in patients who are adherent to treatment with all four drugs compared with patients who are adherent to any combination of three, two or one drug, or no drug; 2) to assess the relationship between baseline sociodemographic and clinical characteristics and adherence to drug therapy; 3) to compare the number of days on sickness leave due to any cause according to adherence to drug therapy; 4) to estimate prevalence of use of the four drug treatments; and 5) to describe the posology prescribed for the four drug treatments.

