### Study Period

Inclusion period was between 2006-2015. The follow-up period was up to 2016.

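### The sick-leave comparison has no counting window of its own; on the only follow-up defined, it includes leave for the index ACS and overlaps the eight months in which adherence is measured

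*Protocol article*

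**What the plan says.** All references are to the Protocol article.

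- **Secondary Endpoints** names the "overall number of days on sickness leave due to any cause and due to CVD events". It gives no start or end of counting and does not set aside leave for the index event.
- **Introduction**, secondary objective 3, is "to compare the number of days on sickness leave due to any cause according to adherence to drug therapy".
- **Study Population** fixes time zero: "Index date definition: date of ACS episode". It requires only two months of follow-up after that date.
- **Primary Endpoint** gives the explicit start of follow-up: "From the index date (first episode of ACS), patients will be followed up to the end of follow-up".
- **Adherence Definition** uses the same origin: "we will calculate the PDC for all four study treatments during eight months of follow-up after the index date". A patient is adherent to a drug with "at least six packages during the first eight months after the event".
- **Study Period**: "The follow-up period was up to 2016", with inclusion in 2006-2015.
- **Statistical analysis** assigns the sick-leave objective to generalized linear models and mentions no landmark, lag or time offset. Adjusted estimates are mentioned only for the Cox hazard ratios.
- **Other Variables** lists potential confounders in relation to the composite endpoint. Among the variables that follow are type of index event and coronary angioplasty.
- **Data Collection and Data Sources** shows that SIDIAP holds dates of sick leave.

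**The concern.** For a patient in work, the index ACS is likely to open a spell of leave at or near day 0. How long it lasts depends in part on how severe the event was and how it was treated. Adherence is not settled until month eight. If leave is totalled from the ACS date, outcome and exposure accrue over the same months, and part of the outcome arises before a patient could have collected six monthly packages.

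Objective 3 would then mix two quantities: convalescence from the event that brought the patient into the cohort, and leave that came after the adherence pattern was established. Only the second can be related to adherence in the right time order. A difference between groups could arise, in either direction, because their index events differed. A genuine later difference could be diluted by variation in the index spell.

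**Working it through.** **Plan's own figures.** Six packages over eight months is 6/8 = 75%, as stated. The expected case count also reproduces: 3415 / 3 years x 10 years x 0.30 = 3415, against about 3400. Neither bears on this point, and no figure is given for sick leave.

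**Step 1: time origins.** The index date is the ACS date. Follow-up for the primary endpoint and the adherence window both start there. If leave is counted over that follow-up, months 0-8 belong to both exposure and outcome.

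**Step 2: size of the overlap.** Assume uniform entry from January 2006 to December 2015, follow-up to December 2016 and no earlier exit. Follow-up T then runs from 12 to 132 months, and the overlapping share is 8/T.

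- T = 12: 8/12 = 67%
- T = 132: 8/132 = 6%
- Average of 8/T over uniform T: (8/120) x ln(132/12) = 16%
- Patients followed for eight months or less, whom the two-month entry rule admits: 100%

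**Step 3: share of total leave due to the index spell.** The inputs are assumptions. The index spell is L = 60 to 180 days, later leave is r = 5 to 30 days per year from month eight, and there is no other leave before month eight.

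Share = L / (L + r x (T - 8)/12)

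| T (months) | Lowest (L = 60, r = 30) | Highest (L = 180, r = 5) |
|---|---|---|
| 12 | 60/(60 + 10) = 86% | 180/(180 + 1.7) = 99% |
| 72 | 60/(60 + 160) = 27% | 180/(180 + 26.7) = 87% |
| 132 | 60/(60 + 310) = 16% | 180/(180 + 51.7) = 78% |

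The index spell can therefore be a minority or a majority of total leave, depending on length of follow-up and the assumed values.

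**Step 4: a difference with no effect of adherence.** Take T = 72, L = 90 in the reference group, and an index spell 10 days longer in the other group for reasons of severity. Later leave is the same in both.

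- r = 5: (100 + 26.7)/(90 + 26.7) = 1.09
- r = 30: (100 + 160)/(90 + 160) = 1.04

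Counting only later spells gives 1.00 in both cases. The 10 days are also an assumption; a difference of the opposite sign would push the ratio below 1.

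**Step 5: would an offset alone suffice?** No, because the index spell is concentrated at the start. With L = 90 and r = 15, the rate is (90 + 5)/1 = 95 days per year at 12 months of follow-up and (90 + 80)/6 = 28 at 72 months, although the later rate is identical. Groups with different follow-up would differ for that reason alone.

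**The case against.** The strongest objection is that the sick-leave window is simply not stated. The explicit index-date start sits under the primary endpoint, and a condensed article may leave the counting rule to the full protocol. It follows that counting from the ACS date is a strong inference, not a quoted rule. The objection does not dispose of the point: it is the only follow-up the article defines, every mention of follow-up uses that origin, and an *overall* total excludes nothing.

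Second, leave due to CVD events could mean new events only, since it follows a list of outcome events and the primary endpoint requires a new diagnosis. That reading is open for the CVD count. It does not help the any-cause count, which is the one objective 3 names.

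Third, type of index event and angioplasty are recorded and could be adjusted for. They are coarse markers of severity, are introduced as confounders for the composite endpoint, and would not remove the overlap in time.

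Three stronger readings are tempting and are not supported:

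- A reader might infer that the comparison mainly reflects index severity. The documents give no leave figures, and the index spell is only 16% of the total at the low end above.
- A reader might infer that some of this leave precedes the adherence window. It does not: that window opens on the index date, so the overlap is during it.
- A reader might infer that the plan treats leave as a consequence of adherence. Its wording is of comparison and association, and its directional hypothesis covers MACE and mortality, not sick leave.

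**Conclusion.** The point holds in limited form. Followed as written, the article leads to a comparison in which leave for the index ACS is part of the outcome and the first eight months serve as both exposure and outcome period. Leave from that period cannot be read as following from adherence.

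The overlap itself rests on the text, given the inference that sick leave shares the only follow-up defined. Its effect on the estimate is not known in size or direction. The 16-99% range for the index share and the null ratios of 1.04 to 1.09 depend wholly on assumed day counts, and the ratios also on an assumed 10-day group difference. The matter affects one secondary objective and leaves the primary analysis untouched, but it is worth correcting because the correction is simple.

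**What to change.** In secondary objective 3 and under Secondary Endpoints, state that the adherence comparison counts only sick-leave days from spells that start after the end of the eight-month adherence window, in patients still under observation at that point. Use follow-up time from month eight as offset in the generalized linear model. Selecting on the start date of the spell also keeps out an index spell that runs past month eight. Report index-ACS leave, and other leave before month eight, separately as description. State whether CVD leave means new events only.

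The cost is a sentence or two and a date filter on data that SIDIAP already holds. The downside is that early leave, including leave for early recurrent events, and patients with under eight months of follow-up drop out of this one comparison. The descriptive report keeps the early leave visible.

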### Other Variables

All the following variables will be considered as potential confounders or effect modifiers in the association between adherence to the drug therapy and risk of the composite endpoint. They will be captured from SIDIAP database:

#### Patient Baseline Characteristics

All sociodemographic characteristics will be measured on the index date: index year, number of visits to PHC, age, sex, MEDEA index (socioeconomic deprivation index) [27], smoking status, alcohol intake, height, weight, Body Mass Index (BMI); the information comes primarily from a codified variable. If the patient has no information, it is calculated from height and weight and physical activity.

**Table 3 table3:** ICD-10 codes for comorbidities of interest or diseases for exclusion

ICD-10 code	Description
I24*, I25*	Coronary heart disease
I63*, I65*, I66*, I67.2, I67.8	Ischaemic stroke
G45	Transient cerebral ischaemic attack
I70*, I73*, I74*	Peripheral vascular disease
E78*	Dyslipidaemia
I10*, I15*	Hypertension
E10*, E11*	Diabetes mellitus
I48	Atrial fibrillation
I50*	Heart failure
C00*-C97*	Malignancies
J40*-J44*	Chronic obstructive pulmonary disease
F30*-F39*	Depression
M05*, M06*, M15*-M19*	Arthritis (osteoarthritis or rheumatoid arthritis)
M80*, M81*	Osteoporosis
N18*	Chronic kidney disease
B20*-B24*	HIV
G30*, G31*	Alzheimer’s disease, other dementias

#### Comorbidities and Clinical Parameters

They will be measured closest to the index date: type of cardiovascular event at index date (AMI and unstable angina and other forms of ACS captured from CMBD-HA), presence of coronary angioplasty implant after the event (data source CMBD-HA), cholesterol and other lipid parameters (low density lipoprotein-cholesterol, high density lipoprotein-cholesterol, total-cholesterol, and triglycerides), blood pressure measured (systolic and diastolic blood pressure), glycated hemoglobin, glomerular filtration rate, serum creatinine, specific comorbid conditions (see ICD-10 codes in Table 3), Charlson comorbidity index [28,29].

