### Data Collection and Data Sources

Diagnoses for study inclusion and endpoints will be obtained from CMBD-HA, which contains diagnoses at hospital discharge from all ICS hospitals, coded with International Classification of Diseases, Nineth Revision (ICD-9) [14]; see Table 1.

The rest of the variables will be captured from SIDIAP, which contains anonymized clinical information of all 279 PHC centres managed by the ICS in Catalonia (North-East Spain), covering a population of more than 5.8 million patients (about 80% of the total of 7.5 million population in Catalonia). The information contained in SIDIAP is registered by PHC general practitioners (GP), nurses and administrative staff in ECAP (electronic health records in ICS): comprehensive sociodemographic information, health conditions registered as ICD10 codes [15], specialist referrals, clinical parameters, toxic habits, PHC laboratory test results, GPs prescriptions and their corresponding pharmacy invoice data registered as Anatomical, therapeutic, chemical classification system (ATC) codes [16], date of sickness leave due to any cause, and date of death. Several reports have shown that SIDIAP data is useful for epidemiological research [17-25]. SIDIAP is listed under the European Network of Centres for Pharmacoepidemiology and Pharmacovigilance (ENCePP) resources database [26].

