### Variables

#### Exposure Definition

Patients will be classified as “exposed” to the study drugs (antiplatelet agents, beta-blockers, ACEI or ARB, statins) if they are prescribed any of them after the episode of ACS (up to two months after the event). The dose prescribed in ECAP will be considered the daily dose used for the patient, and the number of tablets contained in each package will cover the same number of days (see drugs of study in Table 2).

**Table 1 table1:** International Classification of Diseases, Nineth Revision (ICD-9) codes for endpoints of study and procedures.

ICD-9 code	Description
411*	Unstable angina and other forms of acute coronary heart disease
410*	Acute myocardial infarction
433*, 434*, 435*, 436*, 437*	Ischaemic stroke
00.66, 36.03, 36.09, 39.50	Coronary angioplasty

**Table 2 table2:** Anatomical, therapeutic, chemical classification system (ATC) codes for drugs of interest.

ATC code		Description of therapeutic group

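### Comorbid confounders are defined from primary-care codes only, so conditions coded only at the index discharge, and bypass surgery, are missed and part of index severity may remain in the adjusted hazard ratio

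*Protocol article*

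**What the plan says.** Protocol article, Data Collection and Data Sources, splits the sources. "Diagnoses for study inclusion and endpoints will be obtained from CMBD-HA, which contains diagnoses at hospital discharge from all ICS hospitals", coded in ICD-9. "The rest of the variables will be captured from SIDIAP", where primary-care staff enter "health conditions registered as ICD10 codes".

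Other Variables introduces the covariates: "All the following variables will be considered as potential confounders or effect modifiers" of the association between adherence and the composite endpoint. It then gives one source for them: "They will be captured from SIDIAP database".

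Comorbidities and Clinical Parameters lists "specific comorbid conditions (see ICD-10 codes in Table 3), Charlson comorbidity index". It names CMBD-HA as the source for two items only: the type of index event (infarction, or unstable angina and other forms) and coronary angioplasty after the event. Table 3 is an ICD-10 list, and no ICD-9 counterpart is given for comorbidities. In Table 1 the only procedure row is "Coronary angioplasty".

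**The concern.** The case definition in Study Population requires an acute coronary syndrome registered in CMBD-HA, so a discharge record exists for every patient, and the plan already reads two covariates from that dataset. The comorbidity definition does not use its other diagnoses. A condition first recognised at the index admission counts as present only if primary care also records it.

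Severity at the index admission can affect both whether all four drugs are refilled for eight months and the risk of death or recurrence. The Discussion relies on adjusted Cox models to limit confounding, and such models adjust only for what is measured. Recording after discharge may also depend on how closely a patient is followed in primary care, which could itself go with refilling. That link is an inference, not something the document states. The number of primary-care visits is a covariate, but it is measured on the index date and does not describe later contact. The index discharge diagnoses do not depend on that later contact.

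**Working it through.** **What is captured, and from where.** The plan gives no figure on this point, so the check starts by setting its sections side by side.

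| Item | Source in the plan | Consequence |
|---|---|---|
| Infarction vs other index event | CMBD-HA | Adjusted |
| Coronary angioplasty | CMBD-HA | Adjusted |
| Heart failure (I50*), kidney disease (N18*), atrial fibrillation (I48), diabetes (E10*, E11*) | SIDIAP, ICD-10 | Adjusted if primary care records it |
| Glomerular filtration rate, creatinine, glycated haemoglobin, blood pressure | SIDIAP | Adjusted where measured |
| Diuretics, anticoagulants, diabetes drugs, digoxin and antiarrhythmics, nitrates (Table 2) | Pharmacy invoices | Partial proxies |
| The same conditions coded only at the index discharge | Not used | Scored absent |
| Bypass surgery | No code, no source | Same as no revascularisation |

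**How large the residual could be.** Every input below is an assumption; none is in the document. The formulas are the usual approximation for an omitted binary confounder. They do not condition on the planned covariates, so they tend to overstate what would remain.

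*Calculation A.* A condition is missed entirely by primary care, with prevalence p1 in adherent and p0 in nonadherent patients and hazard ratio g for the composite. With no true adherence effect, the observed HR is (1 + (g − 1)p1) / (1 + (g − 1)p0).

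- g = 1.5, 4% vs 6%: 1.02 / 1.03 = 0.990
- g = 2.0, 5% vs 9%: 1.05 / 1.09 = 0.963
- g = 3.0, 6% vs 12%: 1.12 / 1.24 = 0.903

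*Calculation B.* Primary care captures a fraction s of true cases, equally in both groups and with no false positives. Among patients recorded as free of the condition, the remaining prevalence is q = p(1 − s) / (1 − ps), and q replaces p in the formula above.

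Worked case with p1 = 10%, p0 = 20%, s = 50%, g = 2:
- q1 = 0.05 / 0.95 = 0.0526
- q0 = 0.10 / 0.90 = 0.1111
- factor = 1.0526 / 1.1111 = 0.947

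Range over g = 1.5 to 3:

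| Prevalence, adherent vs nonadherent | s = 80% or 50% | s = 0 |
|---|---|---|
| 10% or 15% vs 20% | 0.90 to 0.99 | 0.86 to 0.98 |
| 20% vs 15% | 1.01 to 1.05 | 1.02 to 1.08 |

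**Scale against a cited result.** The Introduction cites a post-infarction cohort with an adjusted HR of 0.81 (95% CI 0.69 to 0.94) for full versus partial adherence. Suppose this study obtained the same result.

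- Dividing by 0.963 gives 0.84 (0.72 to 0.98).
- Dividing by 0.903 gives 0.90 (0.76 to 1.04).
- Dividing by 1.05 gives 0.77.

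Of the two downward factors, only the extreme one moves the interval across 1.

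**The case against.** The plan names a source for each covariate and contradicts nothing, and a condensed article may leave code lists to the full protocol. Much of index severity is already covered: event type and angioplasty from the discharge record, the Table 3 conditions, renal function, and the Table 2 drugs, which need no diagnosis code and bear on heart failure, atrial fibrillation and diabetes. Comorbidities are taken at the record nearest the index date, which does not bar a primary-care entry made after discharge, and eligibility requires at least two months of follow-up in SIDIAP. The bias figures rest wholly on outside assumptions, most of them give a factor close to 1, and there is no estimate at all for bypass.

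Most of this stands, and it limits the point. A reader might infer that heart failure and renal disease are ignored and that index severity as a whole stays in the hazard ratio. The covariate list does not support that. A reader might also infer that the bias must favour adherence, the result the article expects. The document gives no prevalence by adherence group, and the calculation falls on either side of 1. A reader might further take bypass codes to be already in hand. The article describes CMBD-HA as a dataset of discharge diagnoses, and angioplasty is the only procedure it says is taken from there, so the availability of bypass codes is an inference.

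The remaining objection, that this is only missing detail, does not succeed. The article states which source defines the comorbidities, and that choice leaves out diagnoses from the dataset through which every patient is identified.

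**Conclusion.** The point holds as a limited weakness in how the covariates are defined. Conditions coded only at the index discharge are scored absent, bypass surgery is not distinguished from no revascularisation, and part of index severity may therefore remain in the adjusted HR.

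The size and sign of the effect cannot be derived from the document. With partial capture by primary care and the assumed inputs, the factor is about 0.90 to 0.99 if nonadherent patients carry more of the missed condition, and 1.01 to 1.05 if adherent patients do. The effect may well be small. The change is worth making because it is cheap and removes a doubt that would otherwise remain when the main result is read.

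**What to change.** In Other Variables and in Comorbidities and Clinical Parameters:

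1. Score each Table 3 condition used as a confounder as present if it is recorded in SIDIAP under the existing timing rule, or listed as a diagnosis on the index CMBD-HA discharge record through ICD-9 equivalents.
2. Compute the Charlson index from both sources.
3. Where CMBD-HA procedure fields allow, replace the angioplasty indicator with index-admission revascularisation in three levels (none, angioplasty, bypass), and add the ICD-9 bypass codes to Table 1.
4. Enter these variables in the adjusted Cox models, and report the HR with SIDIAP-only comorbidities as a sensitivity analysis.

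The cost is an ICD-9 code list, a merge and possibly a further field request. One drawback is that discharge codes mix acute conditions of that admission with chronic ones; the sensitivity analysis shows how much the choice of source matters.
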